### Procedure

Eligible students will be invited to participate via a website specific to the study, where they will find detailed information about the study procedures. Participants will be asked to provide electronic informed consent before completing an anonymous screening questionnaire to assess their eligibility. The questionnaire is hosted online on the LimeSurvey platform [30]. Participants who meet all inclusion criteria will continue with the baseline assessment (T0) (Figure 1). Those who do not meet the inclusion criteria will be informed that they are not eligible to participate. Participants will complete the intervention and all assessments online.

### Randomization and Blinding

Prior to recruitment, a computer-generated randomization sequence will be created using R [31,30] with a 1:1 allocation to the intervention group and waitlist control group. Simple randomization without blocking or stratification will be used. Participants will be added sequentially to the pregenerated randomization sequence by the personnel responsible for enrollment. For procedural reasons, participants will be randomized before all inclusion and exclusion criteria have been fully verified, as group-specific access links must be provided immediately after successful screening. In the event of a screening failure, the next eligible participant will replace the excluded individual. Once enrolled, the intervention and all subsequent outcome assessments will be made available automatically on the study platform. Automated email reminders to fill in outcome assessments at T1 and T2 will be programmed at enrollment. Investigators do not interact with participants regarding allocation. The personnel enrolling participants have access to the randomization list solely for the purpose of sequentially adding participants. They do not have any influence over assignment beyond adding participants to the list. After a participant is added, allocation, intervention delivery, and outcome assessments are fully automated, preventing any post-enrollment influence by investigators. Participants are not explicitly informed of their group assignment, although they may infer it from the information provided during the informed consent process. As the intervention and outcome assessments are fully automated, no blinding of investigators is required. The data analyst responsible for statistical analyses will remain blinded to group allocation, with group labels coded to ensure that the data analyst is unaware of which condition corresponds to the intervention or waitlist control group during data analysis.

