### Adherence, Retention, and Discontinuation

Access to the intervention will be provided to participants in the intervention group directly after enrollment in the trial. Participants in the waitlist control group will receive access to the intervention after the completion of the final follow-up assessment (T2). No additional measures will be implemented to enhance adherence due to the single-session, automated, and self-guided nature of the SSI, and no ongoing investigator involvement will be required.

Several strategies will be used to promote participant retention. First, the overall time burden of the intervention and outcome assessments is less than an hour. Second, the follow-up intervals are short, with assessments conducted 24 hours and 7 days after the intervention. Third, participants will receive automated reminders to complete the outcome assessments at each follow-up assessment. Finally, participants will be offered the opportunity to enter a raffle as compensation for their participation.

Participants may withdraw from the trial at any time without consequences. No further data will be collected from participants after withdrawal. No investigator-initiated withdrawal will occur unless participants actively request withdrawal. Participants who discontinue the intervention or request withdrawal will be classified as dropouts, as the intervention cannot be adapted, modified, or resumed once discontinued. Loss to follow-up at each assessment time point, including T2, will be recorded.

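### Allocation concealment is not assured: enrolling staff have access to the pregenerated list, and people can be excluded and replaced after assignment without a stated arm-blind eligibility decision

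*Protocol article*

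**What the plan says.** All the main facts stand in the protocol article under Randomization and Blinding.

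- The sequence exists in advance: "Prior to recruitment, a computer-generated randomization sequence will be created using R", with 1:1 allocation. "Simple randomization without blocking or stratification will be used".
- The people who enrol also work the list: "Participants will be added sequentially to the pregenerated randomization sequence by the personnel responsible for enrollment".
- They have access to it: "The personnel enrolling participants have access to the randomization list solely for the purpose of sequentially adding participants".
- Assignment comes before eligibility is settled: "participants will be randomized before all inclusion and exclusion criteria have been fully verified". The reason given is that group-specific links have to go out as soon as screening has been passed.
- Ineligible people leave after assignment: "In the event of a screening failure, the next eligible participant will replace the excluded individual".

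The section offers three safeguards: list access is for one purpose only, staff can influence assignment only by adding people, and everything after that step is automated. The data analyst is also blinded through coded group labels.

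Three other sections bear on the point. Procedure lets only those who meet the inclusion criteria go on from screening to T0. Recruitment and Eligibility Criteria says that eligibility data come from self-report questionnaires. Sample Size counts only people who passed screening and fixes 86 randomised per group.

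**The concern.** Concealment protects the moment at which a person is entered. Whoever enters people should not be able to learn the next assignment beforehand, and entry should be irreversible once the assignment is known. Here the list is made in advance, accessible to the people who enter participants, and followed by a step at which an assigned person can be removed and replaced.

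Two routes to selection bias are left open. The order or timing of adding people could be chosen with the next assignment known. A screening failure could also be declared, or overlooked, with the arm known. If a replacement takes the vacated list position, its arm is known to anyone with access to the list.

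Later steps do not repair either route. Automation starts only after a person has been added, and a blinded analyst works on groups that are already formed. The primary analysis is complete-case per-protocol, which adds further exclusions after randomisation. An intention-to-treat sensitivity analysis is planned, but the article does not say whether replaced screening failures enter it.

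**Working it through.** **Step 1. The plan's own figure.** Sample Size gives a two-sample t test with two-sided alpha 0.025, power 0.80, d = 0.5 and 1:1 allocation. The noncentral t calculation gives 77.3, so 78 per arm and 156 in total, with power 0.804. The stated 156 is reproduced, and this point does not dispute it.

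**Step 2. Each safeguard against what concealment needs.**

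| Stated safeguard | Hides the next assignment from the enroller? | Makes exclusion blind to arm? |
|---|---|---|
| Access for one purpose only | No, it states intent | No |
| No influence other than adding people | No, adding is the step to protect | No |
| Automation after a person is added | No, it starts too late | Not stated |
| Blinded analyst | No | No |

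**Step 3. Order of steps.** Procedure puts screening before T0. Randomization and Blinding sends links after successful screening, yet randomises before all criteria are verified. Sample Size counts only those who passed screening and equates them with those randomised. These cannot all describe one sequence without a further explanation. Since eligibility rests on self-report, the article gives no clear reason why some verification must follow assignment.

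**Step 4. The fixed 86 per group.** Under simple randomisation the number in one arm is binomial with n = 172 and p = 0.5.

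- P(exactly 86/86) = C(172, 86) / 2^172 = 0.061
- P(arms differ by 10 or more) = 0.49
- 95% range for one arm: 73 to 99

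Reaching 86 in each arm therefore needs some further mechanism, such as recruiting until each arm is full or steering through replacements. If one arm fills first, the remaining assignments are predictable even with a hidden list. The equal split buys little: at 73/99 the effective size per arm is 2 x 73 x 99 / 172 = 84.0, against 86.

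**Step 5. Illustrative size of bias.** The article gives no screen-failure rate, so both inputs are assumptions. Let f be the share of one arm selectively removed and g the gap in SD between those removed and those remaining. The full-arm mean is (1 - f) x m + f x (m - g) = m - f x g, where m is the mean of those remaining. The bias is therefore f x g. The last column is the rejection rate of the two-sided 0.025 test with 78 per arm when there is no true effect and the standardised difference equals the bias.

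| f | g | Bias (SD) | Share of d = 0.5 | Type I error |
|---|---|---|---|---|
| 2% | 0.5 | 0.010 | 2% | 0.025 |
| 2% | 1.0 | 0.020 | 4% | 0.026 |
| 5% | 0.5 | 0.025 | 5% | 0.027 |
| 5% | 1.0 | 0.050 | 10% | 0.032 |
| 10% | 0.5 | 0.050 | 10% | 0.032 |
| 10% | 1.0 | 0.100 | 20% | 0.054 |

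For scale, the standard error of the difference at 78 per arm is sqrt(2/78) = 0.16 SD. The 10% row means about 9 of 86 people removed selectively from one arm (0.10 x 86 = 8.6).

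**Step 6. What can still be protected.** 172 - 67 = 105 places were open on 15 April 2026.

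**The case against.** The strongest defence is that the procedure leaves little room for discretion. People enter through a website, and most criteria are fixed and self-reported: age, current treatment, and cut-offs on the DASS-21 stress and depression scales and item 21. Removing people on answers given before randomisation, by the same rule in both arms, does not bias the comparison. This stands. It lowers the likely size of the problem and is why a blanket ban on excluding ineligible people would go further than needed. It does not supply concealment, and the article does not say that the rule is applied automatically or blind to arm.

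Three stronger readings are tempting but not supported.

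- A reader might infer that the list is open and that enrollers see the next assignment. The text says only that they have access. It also calls allocation automated once a person is added, so visibility is unclear. The fair charge is that concealment is not assured.
- A reader might infer that enrollers decide who is a screening failure. No section says who decides.
- A reader might see a contradiction with Adherence, Retention, and Discontinuation: "No investigator-initiated withdrawal will occur unless participants actively request withdrawal". That sentence concerns withdrawal of people in the trial. A screening failure is a different category, which Sample Size does not count toward the target.

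The size is also open to challenge. Even the top of the assumed range is below one standard error, and frequent, strongly selective exclusion is needed to reach it. That is a fair limit on severity. However, a larger sample would not shrink such a bias, and steering before assignment cannot be corrected in the analysis.

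**Conclusion.** The point holds: as written, the plan permits selection bias at entry and at post-randomisation exclusion, and no stated safeguard closes either route. This is a consequence of what the article states, not of detail left to another document. The article does not show that any assignment was steered or any exclusion was selective.

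Under the assumed inputs (2-10% of one arm removed, a gap of 0.5-1 SD) the bias is about 0.01-0.10 SD, or 2-20% of the planned effect. These inputs have no source in the documents, and the range covers selective exclusion only. Steering of entry is not quantified. The 0.06 probability of an 86/86 split assumes simple randomisation of exactly 172 people.

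This should be fixed. It falls short of a fatal flaw because fixed self-reported criteria limit discretion and the plausible bias is modest.

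**What to change.** For the participants still to be enrolled:

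1. Score the self-reported criteria and have T0 submitted first. Only then release the next assignment and the group link, through the platform or through an existing team member who is not involved in enrolment.
2. Remove enrolling staff's access to unused assignments.
3. Do not reuse a vacated list position. A later entrant takes the next unused assignment.
4. Judge any ineligibility found later only on pre-randomisation data, by someone blind to arm, and name that role.
5. Report exclusions after randomisation by arm with reasons, including those already made. Include these people in the planned intention-to-treat sensitivity analysis where data exist.
6. Reconcile Procedure, Randomization and Blinding, and Sample Size on the order of screening, T0 and assignment. Either state 172 as a total and accept the split that simple randomisation gives, or describe how 86 per group is reached without making late assignments predictable.

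The cost is a small procedural change with an amendment to the ethics and registry records, and a few ineligible people in the sensitivity analysis. Screening and intervention run on separate platforms, and the article does not show whether they can be linked for automatic release. If they cannot, release by a separate team member achieves the same end but may delay the link. Assignments already made cannot be concealed in retrospect; for those, reporting by arm is what remains.

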### Recruitment and Eligibility Criteria

The participants will be university students from German-speaking universities in Switzerland. The trial will be advertised on German-speaking universities’ campuses through flyers and brief announcements in teaching formats, as well as institutional newsletters and social media channels of the participating universities. In addition, targeted social media advertisements will be used. Interested individuals will be directed to a study-specific website hosted by the Swiss provider Infomaniak [32], where they will receive detailed information on how to enter the trial.

To be eligible for participation, individuals (1) must be healthy students enrolled at universities in German-speaking Switzerland, (2) be between 18 and 65 years of age, (3) be fluent in German, (4) not be currently undergoing psychological or psychiatric treatment, (5) have a score >7 on the DASS-21 stress scale, and (6) be willing to participate in the study. Participants will be excluded if they (1) are currently in psychological or psychiatric treatment, (2) have insufficient German language skills to understand study instructions, or (3) score ≥10 on the DASS-21 depression scale and/or ≥2 on item 21 (“I felt that life was meaningless“) during screening. These data will be collected through self-report questionnaires, including questions such as: “Are you currently undergoing psychotherapy?” to check for inclusion criteria (4).

### Rationale and Development of the Intervention

The compassion-focused online SSI was developed specifically for this study to address academic stress among university students. Grounded in the theoretical framework of CFT [19,33], the intervention draws upon evidence-based psychoeducational and experiential techniques. The content was developed based on previous research into stress management in higher education settings and by established CFT protocols. The study team created and recorded all materials, including video content, guided audio exercises, and written instructions, with support from the New Media Center of the University of Basel. Two members (CW and SZ) of the study team were Master’s students, and additional Master’s students pilot-tested the intervention, providing feedback that was used to adapt and further refine the content. Materials were then pilot-tested internally to ensure clarity, accessibility, and engagement .

### Delivery Platform

The intervention is delivered online via a study-specific website hosted by the Swiss provider Infomaniak. Participants receive a personal access code via email, granting them entry to the intervention platform. All content is self-guided and designed to be completed in a single 45-minute session, with no involvement from a live facilitator. The process is fully automated, enabling participants to proceed at their own pace while following the structured sequence of components.

### Components of the SSI

#### Intervention Structure

The intervention comprises 3 sequential modules consisting of a psychoeducational component, an experiential component, and a final reflection and action planning phase (Figure 2 for an overview of the intervention), in accordance with the structure of other SSIs [24,34-36].

**Figure 2. F2:**
[figure not shown]
Screenshots of the intervention.

#### Psychoeducational Component

The session begins with a 3-minute animated explainer video [37] that introduces the concept of academic stress and its psychological impact. The video draws on current research on stress and student well-being [38]. Participants are then invited to reflect briefly on their own experiences of academic stress, a process expected to take them 3 minutes (see supplementary material, available on the Open Science Framework [39]).

Participants are then introduced to the core principles of CFT with a prerecorded 6-minute video from the author OB, who is a CFT specialist and licensed psychotherapist. In the video, the 3-circle model of emotion regulation (threat, drive, and soothing systems) and the role of compassion in managing self-criticism and distress are explained, combining theoretical background from evolutionary psychology, neuroscience, and clinical research. Next, participants are asked to spend about 3 minutes reflecting on their personal experiences of compassion.

#### Experiential Component

In the experiential component, participants complete a guided 5-minute soothing rhythm breathing exercise, during which they adopt and practice a compassionate body posture and a calm breathing rhythm. This exercise is followed by 1 of 3 compassion imagery exercises (compassionate color, compassionate self, or compassionate friend) to practice self-compassion skills, which will take approximately 6 minutes. All exercises will be provided to the participants in audio and written formats, enabling participants to select their preferred method (screenshots of the intervention are shown in Figure 2). Finally, participants are asked to reflect for about 3 minutes on the intervention session in its entirety.

#### Reflection and Action Planning

After the experiential activities, participants receive a PDF “Action Plan” summarizing key psychoeducational points and specific strategies for applying self-compassion in situations of academic stress. The Action Plan also contains information on further mental health resources. The corresponding materials will be uploaded upon publication of the study on the Open Science Framework [39]. Participants can access all intervention components at any time after completion using their personal access code.

### Control Group

Participants allocated to the waitlist control group will not receive the intervention until they have completed all the study assessments (T0, T1, and T2). They complete the same questionnaires as the intervention group at the same time points, enabling direct comparisons between the 2 groups.

### Adherence, Retention, and Discontinuation

Access to the intervention will be provided to participants in the intervention group directly after enrollment in the trial. Participants in the waitlist control group will receive access to the intervention after the completion of the final follow-up assessment (T2). No additional measures will be implemented to enhance adherence due to the single-session, automated, and self-guided nature of the SSI, and no ongoing investigator involvement will be required.

Several strategies will be used to promote participant retention. First, the overall time burden of the intervention and outcome assessments is less than an hour. Second, the follow-up intervals are short, with assessments conducted 24 hours and 7 days after the intervention. Third, participants will receive automated reminders to complete the outcome assessments at each follow-up assessment. Finally, participants will be offered the opportunity to enter a raffle as compensation for their participation.

Participants may withdraw from the trial at any time without consequences. No further data will be collected from participants after withdrawal. No investigator-initiated withdrawal will occur unless participants actively request withdrawal. Participants who discontinue the intervention or request withdrawal will be classified as dropouts, as the intervention cannot be adapted, modified, or resumed once discontinued. Loss to follow-up at each assessment time point, including T2, will be recorded.

### Outcomes

All outcomes will be collected online. Basic demographic data (age, gender, and academic level) will be collected at baseline (T0). Change in perceived stress, the primary outcome, will be assessed using the difference score of the stress scale of the German version of the DASS-21 [40], measured at baseline (T0) and at 1-week follow-up (T2). The stress scale of the DASS-21 consists of 7 items rated on a 4-point Likert scale (0 = “did not apply to me at all” to 3 = “applied to me very much or most of the time”), yielding total scores from 0 to 21 for the difference score. Higher difference scores indicate greater reduction in perceived stress.

The secondary outcomes are the change in depressive symptoms and anxiety. Change in depressive symptoms and anxiety will be assessed using the difference score of the respective DASS-21 scales, measured at T0 and T2. Each scale consists of seven items, which are rated on the same 4-point Likert scale as the stress scale (total difference score range: 0‐21). The additional exploratory outcome, self-compassion, will be measured using the short version of the German Self-Compassion Scale (SCS-D-KF) [41]. This scale comprises 12 items covering 6 dimensions of self-compassion. Each item is rated on a 5-point Likert scale (1=“almost never” to 5=“almost always”). The scale will be administered at T0, T1, and T2. The primary predictor variable is group allocation (intervention vs. waitlist control), which is assigned through randomization and coded dichotomously (0=control, 1=intervention). No data monitoring committee has been established due to the minimal-risk, single-session, fully automated nature of the intervention. Oversight will be provided by the principal investigators.

### Statistical Methods

Analyses will follow a complete-case per-protocol (CC-PP) approach, including only participants who completed T0, T1, and T2 (complete cases). Inclusion and exclusion criteria for PP are prespecified in the protocol. Linear models in combination with type II ANOVA will be applied to investigate group differences for the primary and secondary outcomes.

The primary outcome is the change in perceived stress (DASS-21 stress scale) from baseline (T0) to 1-week follow-up (T2). Secondary outcomes are (1) change in depression (DASS-21 depression scale) from T0 to T2, and (2) change in anxiety (DASS-21 anxiety scale) from T0 to T2. Group allocation (intervention vs waitlist control) will be included as a between-subject factor.

For the additional outcome self-compassion (SCS-D-KF) (3), which is assessed at T0, T1, and T2, a linear mixed-effects model will be used, including visit (T1 and T2) as a within-subject factor and group as a between-subject factor. Subject ID will be included as a random effect to account for within-subject correlations across visits. Baseline self-compassion (T0) will be included as a covariate to adjust for individual differences at study entry.

Covariates (sex, age, and academic level) will be entered as main effects and as 2-way interactions with group. Nonsignificant interaction terms will be removed from the final model. If significant interactions are detected, post hoc tests will be conducted to explore and describe the effects.

Group differences in change scores of the Visual Analogue Scale stress from T0 to directly after the intervention will be analyzed as a manipulation check to assess whether the intervention produced the expected immediate effect on perceived stress.

Results will be reported as mean (SDs) for the intervention and control groups, 2-sided *P* values, and adjusted between-group differences with 95% CIs. For the secondary outcomes, the significance level will be adjusted using a Bonferroni correction for the number of independent tests. Effect sizes will be expressed as Cohen *d*, derived from the *t* values of the models and adjusted for covariates. By convention, *d*=0.2 will be interpreted as a small effect, *d*=0.5 as a medium effect, and *d*=0.8 as a large effect.

All analyses will be performed using R (version 4.5.X; R Development Core Team) [31].

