### Attrition and Assessment of Potential Bias Under the CC-PP Approach

As the primary analyses follow a CC-PP approach requiring observed data at T0, T1, and T2, potential bias due to attrition will be assessed. Completion rates will be summarized by randomized group and compared using chi-square or Fisher exact tests, as appropriate. Baseline characteristics will be compared between completers and noncompleters, prioritizing the corresponding T0 value of each primary and secondary outcome, using appropriate statistical tests and standardized mean differences.

To formally evaluate differential attrition while accounting for baseline outcome severity, dropout will be modeled separately for each outcome using logistic regression with treatment group as the primary predictor, adjusted for the respective outcome’s T0 value as well as age and sex (dropout ~ group+outcome_T0+ age+sex). If the number of dropout events is insufficient to support covariate-adjusted models, parsimonious models will be fitted as prespecified. Sensitivity analyses under an intention-to-treat framework using linear mixed-effects models with all available repeated measures will be conducted to assess the robustness of the per-protocol findings to different assumptions about missing data.

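### The primary per-protocol set is defined by returned questionnaires with no session-use criterion and conflicts with the dropout rule, so the article does not settle what the primary estimate measures.

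*Protocol article*

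**What the plan says.** Statistical Methods in the protocol article sets the primary analysis: "Analyses will follow a complete-case per-protocol (CC-PP) approach, including only participants who completed T0, T1, and T2 (complete cases". The next sentence adds: "Inclusion and exclusion criteria for PP are prespecified in the protocol". The section on attrition and bias repeats the definition as a "CC-PP approach requiring observed data at T0, T1, and T2". Neither place asks whether a student in the intervention arm started or finished the session. The criteria that the article prints are trial eligibility and the questionnaire rule.

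The section on adherence, retention and discontinuation has a different rule: "Participants who discontinue the intervention or request withdrawal will be classified as dropouts". It does not mention students who never start. On adherence it says: "No additional measures will be implemented to enhance adherence". It also says that controls get access only after T2.

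On timing, that section describes "assessments conducted 24 hours and 7 days after the intervention", while Randomization and Blinding says: "Automated email reminders to fill in outcome assessments at T1 and T2 will be programmed at enrollment".

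The primary outcome is the change in DASS-21 stress from T0 to T2; T1 does not enter it. An intention-to-treat mixed model is planned as a sensitivity analysis.

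**The concern.** A reader takes a per-protocol result to be the effect in people who received the intervention as planned. The printed definition does not select on that. It selects on returning three questionnaires, one of which the primary outcome does not use.

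The dropout rule makes the set ambiguous. It treats stopping the session and withdrawing from the trial alike, and it does not say whether a student who stops the session but keeps answering stays in the analysis. During the trial only one arm has a session to stop, so the answer decides whether the randomised comparison is preserved.

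The same ambiguity reaches the check meant to detect bias. The attrition model has dropout as its outcome and group as its main predictor. If dropout includes stopping the session, one arm has an extra way of becoming a dropout, and the group coefficient no longer describes loss to follow-up alone.

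**Working it through.** **1. The plan's own figure.** Inputs from Sample Size: d = 0.5, two-sided alpha 0.025, power 0.80, 1:1 allocation. Two-sample t test with noncentral t: df = 78 + 78 − 2 = 154, noncentrality = 0.5 × √(78 × 78/156) = 0.5 × √39 = 3.12. Power is 0.804 with 78 per group, so the stated 156 is reproduced.

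**2. The two rules applied to each type of intervention-arm student who returns T0, T1 and T2.**

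| Session use | Questionnaire rule | Dropout rule |
|---|---|---|
| Completed | In | In |
| Stopped part-way | In | Dropout |
| Never started | In | Not addressed |

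The second row is a direct conflict. The third is a gap.

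**3. Reading A: part-way stoppers are removed.** Let a share q be removed from the intervention arm only, with mean change b SD worse than those kept. With no true effect the full arm has mean 0 = (1 − q)m + q(m − b), where m is the mean of those kept. Hence m = q × b, and this is the bias. The documents give neither q nor b, so both are assumed. Rejection rates keep 78 per arm.

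| q | b | Bias (SD) | Rejection at nominal 0.05 | At nominal 0.025 |
|---|---|---|---|---|
| 10% | 0.5 | 0.05 | 6.1% | 3.2% |
| 20% | 0.5 | 0.10 | 9.5% | 5.5% |
| 20% | 1.0 | 0.20 | 23.7% | 15.8% |

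Of 86 randomised per arm, 10% is about 9 students and 20% about 17. Against the planned d of 0.5, the bias is 10% (0.05/0.5) to 40% (0.20/0.5). If stoppers would have done better than those kept, the sign reverses.

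**4. Reading B: part-way stoppers are kept.** The set is then everyone with three questionnaires, compared by assignment. If a share f of intervention-arm completers did not use the session and gained nothing, the contrast is d = 0.5 × (1 − f), taking 0.5 as the effect in users. The documents do not give f. At 78 per arm and alpha 0.025:

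| f | d | Power |
|---|---|---|
| 0 | 0.50 | 0.80 |
| 10% | 0.45 | 0.71 |
| 20% | 0.40 | 0.59 |
| 30% | 0.35 | 0.47 |

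This shows how far a figure labelled per-protocol could lie from the effect in users. Any analysis by assignment would be diluted in the same way.

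**5. Which exposure suits a complier-average estimate.** Assume never-starters of 10%, 20% or 30%, a further 10% part-users with half the effect (0.25), and 0.5 in completers. The effect of assignment is 0.5 × 0.80 + 0.25 × 0.10 = 0.425, then 0.5 × 0.70 + 0.025 = 0.375, then 0.5 × 0.60 + 0.025 = 0.325.

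- Exposure = completion: 0.425/0.80 = 0.53; 0.375/0.70 = 0.54; 0.325/0.60 = 0.54. All exceed the 0.5 in completers, because part-users benefit without counting as exposed.
- Exposure = any start: 0.425/0.90 = 0.47; 0.375/0.80 = 0.47; 0.325/0.70 = 0.46. This is the average effect among starters, full and partial together.

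**The case against.** The strongest objection is that the article points elsewhere. It says that per-protocol criteria are prespecified, and that the trial protocol, with a statistical analysis plan, is registered. Neither is shown, and an exposure rule may be there. That stands: it cannot be claimed that questionnaires are the sole criterion. It does not remove the point, because the article states the set twice in terms of questionnaires and gives a dropout rule that conflicts with it.

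A reader might infer that students who never opened the session count as treated while those who stopped part-way are excluded. The documents do not support this. It needs the dropout rule applied to stoppers but not to non-starters, and no section says so. If the dropout rule governs the set, the set is not defined by questionnaires alone; if it does not, part-way stoppers stay in. Reminders programmed at enrolment make it plausible that a non-starter answers T1 and T2, but no section says how that student is analysed, and follow-up is nominally timed from the intervention.

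A reader might also take the power figures as an error in the sample size. They are not: the non-use share is assumed, and the article does not say that d = 0.5 applies to users only.

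Finally, the planned intention-to-treat analysis does address the effect of assignment. It does so only as a sensitivity analysis, and it leaves the primary set ambiguous.

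**Conclusion.** The point holds in a limited form. As printed, the primary set states no session-use criterion and conflicts with the dropout rule. Removing stoppers who answered everything biases the comparison through exclusions in one arm; keeping them gives a complete-case comparison by assignment under the wrong name.

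The bias of 0.05 to 0.20 SD and the diluted d of 0.45 to 0.35 illustrate the two readings. They rest on assumed shares and prognosis gaps and predict nothing about this trial. If the registered protocol contains an exposure rule, the ambiguity may be resolved there, but the three sections of the article must then be reconciled with it. A rule that removes intervention-arm students for not using the session would carry the same one-sided selection.

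**What to change.** 1. In Statistical Methods and in the attrition section, stop calling the T0/T1/T2 set per-protocol. If the registered protocol has an exposure rule, reconcile these sections and the dropout rule with it.
2. In the same places and in the section on discontinuation, state that stopping or not starting the session does not remove a participant from follow-up or from the analysis. Record session discontinuation separately from withdrawal and loss to follow-up, and use only the latter two as dropout in the attrition model.
3. Analyse the T0 to T2 primary outcome by randomised group in everyone with T0 and T2, whatever their session use and whether or not T1 was returned.
4. Report counts of not started, partly done and completed in the intervention arm, as far as the platform records them.
5. If the effect of receiving the session is wanted, add a supportive complier-average estimate with randomisation as instrument and any session start as exposure. Non-use is one-sided because controls have no access before T2. Completion should not be the exposure, since it overstates the effect when part-users benefit.

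The cost is wording, a changed analysis set and, if wanted, one extra model. The supportive estimate has a wider interval and depends on usage data that the article does not describe beyond a personal access code. With 67 of 172 enrolled on April 15, 2026 and analysis planned for winter 2026, the change can be made before analysis begins.
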